#### Primary and Secondary Outcomes

The primary outcome measure is the Juniper Asthma Control Questionnaire (ACQ). The ACQ provides a reliable and validated measure of the impairment dimension of asthma control [28,31] and includes specific measures of each component of impairment as defined in the current asthma treatment guidelines [22], i.e., daytime and nocturnal asthma symptoms, functional capacity, rescue medication use (excluding use for prevention of exercise-induced bronchospasm), and lung function (FEV1). ACQ is the only composite measure, among the several recommended by the guidelines, that includes lung function in its overall rating and is in widespread use in trials of both asthma pharmacotherapeutic and behavioral interventions [22].

Secondary outcomes include lung function measurements by spirometry (Table 2) and the 15-item Juniper Mini Asthma Quality of Life Questionnaire (mini-AQLQ) [32]. In addition, asthma-related health care utilization (HCU) will be assessed through data extraction from KPNC electronic databases for the period of 12 months pre- and post-randomization. These databases contain information on all outpatient and inpatient HCU at KP facilities, non-KP facilities with which KP contracts for emergency and hospital services, and on reimbursable emergency hospital care at non-contract facilities. Although we will analyze HCU data according to type of encounter, the primary HCU outcome will be the overall rate of outpatient encounters and emergency department and inpatient admissions with asthma as primary diagnosis. Data will also be extracted on current medications prescribed and all asthma, allergic rhinitis, and GERD medications dispensed for the same time periods. In KP, it is estimated that well over 95% of all prescriptions are filled at a KP pharmacy, and patients are very unlikely to have concurrent non-KP sources of asthma care or pharmacy. Therefore, dispensing records provide reliable and unbiased information on medication refill adherence and regimen potency. The former will be assessed by calculating continuous medication acquisition indices (the total days supply of a given type of medication dispensed in a given period of time as a proportion of the total days supply prescribed), for asthma controller and reliever medications separately. The total strength of all controller medications dispensed in a given time period will be expressed in beclomethasone-80 canister equivalents, and the total strength of all reliever medications dispensed in a given time period will be expressed in albuterol canister equivalents, as we have done in our previous research [33]. For combination medications (e.g., fluticasone-salmeterol), each active ingredient component of the medication will be counted separately and all will contribute to the adherence and potency calculations.

Additional secondary outcomes include measurements of waist circumference, hip circumference, and resting blood pressure according to standardized protocols as recommended by the PhenX project https://www.phenx.org). Dyspnea with activities of daily living will be assessed using a baseline dyspnea index to rate severity of dyspnea at a single state and a transition dyspnea index that denotes changes from that baseline [34]. The 12-item Short Form Health Survey (SF-12) [35], a widely used measure of generic health-related QoL, will be administered to evaluate changes in non-disease specific physical and mental health status. The Obesity-Related Problem Scale is a reliable eight-item scale that measures the impact of obesity on psychosocial functioning and is responsive to weight loss intervention [36]. Mental health status will be assessed using the 20-item Center for Epidemiological Studies Depression scale (CES-D) [37] and the Depression Anxiety Stress Scale [38]. In addition to asthma-related HCU, utilization for other obesity-related co-morbidities, non-asthma pulmonary diagnoses, and all other HCU will be assessed.

#### Potential Mediators

The intervention to be studied involves changes in diet and physical activity aimed at producing weight loss. Undoubtedly, there will be variation in changes in weight loss, physical activity level, and diet. Also, some evidence suggests that physical activity and certain nutrients may have independent effects on asthma outcomes [39-44]. Investigating the relative contribution of changes in BMI, physical activity, and diet will provide evidence of whether the underlying mechanism for improvement in asthma control is related to weight loss *per se *or not. Caloric and nutrient intake will be determined from food records collected on two non-consecutive weekdays and one weekend day within a seven-day period at each assessment point. Multiple-day food records are considered a gold standard for collection of individual dietary data [45]. Food composition will be analyzed using the Nutrition Data System. Physical activity will be measured using the Stanford 7-Day Physical Activity Recall, which is a reliable measure that is sensitive to change in physical activity [46-48].

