## Aims

The BE WELL (*B*reathe *E*asier through *We*ight *L*oss *L*ifestyle) intervention trial was designed to address the gap in knowledge of whether weight loss improves asthma control. It aims to evaluate the efficacy of an evidence-based, comprehensive weight loss lifestyle intervention as adjunct therapy to usual care in the management of asthma in obese adults. The primary hypothesis is that compared with participants in the usual care (UC) arm, those in the weight loss intervention (WL) arm will achieve greater improvement in asthma control, as measured by a validated composite measure, the Juniper Asthma Control Questionnaire (ACQ) [28], at 12 months follow-up. Secondary aims include comparing the WL and UC arms on changes in ACQ scores at six months and in lung function, asthma-specific quality of life (QoL), asthma medication use, and asthma-related health care utilization (HCU) at six and 12 months. Potential mediators (e.g. weight loss and change in physical activity level and diet composition) and moderators (e.g., socio-demographic characteristics and comorbidities) of the intervention effects will be explored.

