#### Intervention Format, Structure, and Content

Participants in both the UC and WL arms will continue to receive the standard of medical care from their PCPs and any specialists, per KPNC treatment protocols. In addition, they will receive an Omron HJ-7201ITC pedometer, which records steps taken, and an HBF-400 scale for home weight measurement. They will also receive KPNC standard asthma self-management and weight management educational handouts and a list of elective weight management services offered at the participating medical centers.

In addition to usual care, participants in the WL arm will progress through three successive intervention stages: Intensive, Transitional and Extended stages. Table 3 shows the design elements of the BE WELL intervention during the three stages.

**Table 3 T3:** Design elements of the BE WELL weight loss intervention

Stage	Intensive (Months 1-4)	Transitional (Months 5-6)	Extended (Months 7-12)
**Goal of contact**	Gradual weight loss associated with small, progressive changes in diet and physical activity		Weight maintenance or continued gradual weight loss
**Contact schedule**	Weekly (13 contacts)	Monthly (2 contacts)	Bi-monthly/monthly (typically 3-6 contacts)
**Contact mode**	Group, in person (Family member welcome)	Individual, in person (Family member welcome)	Individual, by phone (in person as needed)
**Contact duration**	90-120 minutes	30-60 minutes	Variable
**Contact structure**	* Private weigh-in * Review and sharing of progress, or lack thereof, in relation to action plan/goals from last session * Didactic presentation of a new topic * 30-minute supervised physical activity session * Development of individual action plan/goals for the next week	* Private weigh-in * Review of self-monitoring records * Identification of personal barriers to weight loss and activity * Problem solving and relapse prevention * Development/revision of a customized care plan	* Review of self-monitoring records * Detection of signs of non-adherence and relapse * Problem solving to encourage adherence and prevent relapse * Revision of the customized care plan * If indicated, re-initiation of intensive weight loss efforts through individual or small group visits

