We will use the MacArthur approach, which modified the Baron & Kenny criteria, for defining moderators and mediators in clinical research studies [69]. Let T be the treatment, M be the potential moderator or mediator, and O be the outcome. Association between T, M, and O is examined using the following models:(4)

M can be considered a mediator of the effect of T on O if T precedes M, γ1 ≠ 0, and either β2 ≠ 0 or β3 ≠ 0. M is a moderator of the effect of T on O if M precedes T, γ1 = 0, and β3 ≠ 0.

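### The protocol promises the relative contribution of weight, activity and diet, but the mediation rule it states assesses one mediator at a time, so correlated changes can each qualify

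*Protocol article*

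**What the plan says.** Under Potential Mediators, the protocol article notes that "some evidence suggests that physical activity and certain nutrients may have independent effects on asthma outcomes". It then says that "Investigating the relative contribution of changes in BMI, physical activity, and diet will provide evidence of whether the underlying mechanism" behind any improvement is weight loss as such or not. The Aims list the candidates as examples, to be explored: "Potential mediators (e.g. weight loss and change in physical activity level and diet composition) and moderators".

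The method comes at the end of Statistical analysis: "Let T be the treatment, M be the potential moderator or mediator, and O be the outcome". M counts as a mediator "if T precedes M, γ1 ≠ 0, and either β2 ≠ 0 or β3 ≠ 0". From the roles these coefficients play in the rule, γ1 is the effect of treatment on M, β2 the association of M with the outcome given treatment, and β3 the treatment-by-M interaction. No other mediation method is given. Equation 4 itself was not in the text available for this review, so the single-M reading rests on the definitions and coefficients in the surrounding prose.

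**The concern.** The aim is comparative: how much of any benefit runs through weight rather than through activity or diet. The stated rule is a yes/no test of one variable, with no other candidate held constant.

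The intervention sets a 7% weight-loss goal, 150 minutes a week of moderate activity and a calorie goal (Evidence-based Intervention Goals). If it works as intended, treatment moves all three, so γ1 ≠ 0 does not separate them. The remaining condition, β2 ≠ 0 or β3 ≠ 0, is then open to confounding between mediators: a candidate with no effect inherits an association from a correlated one that does have an effect.

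The likely result is a list in which BMI, activity and diet each qualify. The error that matters most here is weight being credited with an effect that belongs to activity or nutrients, because that gives the wrong answer to the question the section poses.

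**Working it through.** **The plan's own figure.** The protocol states no figure for mediation. Its completer count reproduces: 324 × 0.8 = 259.2. For d = 0.4, 90% power and two-sided 5%, the usual formula gives 132 per arm, 264 in total and 264 / 0.8 = 330 randomized, against 324. Power at 129.5 per arm is 0.894 (t-test) or 0.896 (normal). The sample size is not at issue.

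**Inputs to the illustration.**
- N = 259 and 1:1 allocation, from the protocol.
- Assumed: treatment shifts weight and activity by 0.6 SD each. Activity affects the outcome with slope b, and weight has no effect. The within-arm correlation of weight and activity is ρ. Residual SDs are 1.
- Rule: T on M significant at 5%, and either M or T×M significant at 5%.

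**Step 1: does weight pass γ1?** z = 0.6 × √259 / 2 = 4.83, so it passes with probability Φ(4.83 − 1.96) ≈ 0.998. This condition filters out almost nothing.

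**Step 2: what β2 estimates with weight alone in the model.** The apparent weight slope is bρ, although the true slope is zero. Its standard error is about √{[1 + b²(1 − ρ²)] / 259}. For b = 0.3 and ρ = 0.3:
- slope 0.09, SE √(1.082/259) = 0.0646, z = 1.39;
- probability significant Φ(1.39 − 1.96) ≈ 0.285;
- adding the 5% chance from the interaction, 1 − 0.715 × 0.95 ≈ 0.32.

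**Step 3: range, with simulation** (2,000 trials per row; 4,000 for the last).

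| b | ρ | bρ | z | Rule, by formula | Rule, simulated | Weight, joint model, simulated |
|---|---|---|---|---|---|---|
| 0.3 | 0 | 0 | 0 | 10% | 9% | 9% |
| 0.3 | 0.3 | 0.09 | 1.39 | 32% | 30% | 10% |
| 0.3 | 0.5 | 0.15 | 2.34 | 66% | 66% | 11% |
| 0.3 | 0.7 | 0.21 | 3.30 | 92% | 90% | 11% |
| 0.5 | 0.5 | 0.25 | 3.69 | 96% | 95% | 10% |

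The joint model holds weight, activity and both interactions with treatment. It still detects activity in 92% to 99.8% of trials. Its floor near 10% is the either/or rule at 5% each: 1 − 0.95² = 9.75%.

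**Step 4: should medication enter as a further parallel mediator?** Suppose the true BMI slope on the outcome is 0.40, medication has no effect, and medication responds to asthma control with slope r (unit residual variances, all assumed). Adding medication changes the BMI slope to 0.40 / (1 + r²). That is 0.40 / 1.25 = 0.32 at r = 0.5, and 0.40 / 2 = 0.20 at r = 1. The cost is bias, not only imprecision.

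**The case against.** **A condensed article may leave the multi-mediator model to the analysis plan.** That would excuse missing detail. Here, however, both an aim and a method are printed, and the method does not deliver the aim. Nothing printed rules out a joint model, which is why the fix is an addition.

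**Activity may be a genuine upstream mediator.** The protocol describes diet and activity changes as directed at weight loss. If activity works by lowering weight, calling it a mediator is correct. This is why the illustration makes weight the inert variable: crediting weight is then wrong, whatever produced the correlation.

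**The numbers are assumed.** This stands. The direction follows from leaving out a correlated true mediator; the size depends on inputs the documents do not give.

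**Stronger readings a reader might infer:**
- *The trial cannot tell whether weight loss per se explains the effect.* Too strong. If treatment does not move a candidate (γ1 = 0), the rule excludes it. It fails in the expected case, where all candidates move.
- *Omitting medication from the mediators is an error.* Not supported. The list in the Aims is open, and medication use is a secondary outcome, so an arm difference would be reported: "Data will also be extracted on current medications prescribed and all asthma, allergic rhinitis, and GERD medications dispensed for the same time periods". Patients in both arms "will continue to receive the standard of medical care from their PCPs and any specialists", under the health plan's treatment protocols, which does not say that controllers may be changed freely. The asthma teaching in the intensive stage concerns exercise-induced bronchospasm, and both arms get self-management handouts. Dispensing over the 12 months can also respond to asthma control.
- *The Discussion's causal claim rests on this analysis.* It is tied to achieving the study's goals generally, and the study of mechanisms is described as future work.

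**Conclusion.** The point holds as a mismatch between a stated aim and the one stated method. The single-M rule gives no relative contribution and, when weight, activity and diet change together, can credit a change that has no effect. Under the assumptions shown, false credit to weight runs from about 30% to about 96% of trials at correlations of 0.3 to 0.5, against about 10% in a joint model.

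This rests on the single-M reading of the text without equation 4, and on assumed shifts, slopes and correlations. It does not extend to medication as a required parallel mediator, nor to a claim that the question is unanswerable. The mediation analysis is exploratory, and the primary comparison of asthma control at 12 months is untouched.

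**What to change.** In the mediation part of Statistical analysis, add one model for the weight-loss-per-se question. It should contain changes in BMI, physical activity and diet together, with baseline covariates. Diet should include calories and the specific nutrients of interest, since the protocol's own concern is about nutrients as well as energy. Report each specific indirect effect with a bootstrap confidence interval, and base the statement about weight loss per se on the BMI-specific effect. Keep the single-M models as descriptive.

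Do not enter medication change as a parallel mediator in the main model. At most, examine it in a sensitivity analysis that says dispensing may respond to asthma control.

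The cost is a few sentences and some programming, because the variables are already collected. Intervals for each path will be wider, which reflects how hard correlated pathways are to separate. A joint model still depends on adjustment for mediator-outcome confounders and on time order, and the report should say so.

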#### Potential Moderators

To elucidate differences in intervention effects among subgroups of the study sample, we will collect data on important socio-demographic characteristics: age, sex, race/ethnicity, education, marital status, household income, medical insurance, smoking status, and age at onset of asthma symptoms. In addition, the Berlin Questionnaire for sleep apnea[49] and the Gastroesophageal Reflux Disease (GERD) Symptom Assessment Scale[50] will be used to screen for possible sleep disorders and GERD, respectively, as these are common comorbidities in obese individuals with or without asthma. Their presence may modify the intervention effect.

#### Process Measures

Data to assess the likelihood of potential subsequent adoption of the weight loss intervention by the health care system, such as the representativeness of physician approval of their patients' participation, patient willingness to enroll in the study, and reasons for declining to participate will be documented. Intervention process measures will include dates and number of classes attended, number and duration of in-clinic visits and phone calls, patient self-monitoring records, and data electronically stored in pedometers provided to participants by the study.

### Interventions

#### Theoretical Basis

The theoretical underpinning of the BE WELL weight loss intervention is derived from Social Cognitive Theory [51] and the Transtheoretical Model of Behavior Change [52]. The former emphasizes the reciprocal determinism between individual, environment, and behavior, whereas the latter recognizes that behavior change is a dynamic process that moves, at variable speed, through stages of readiness to change. Behavior change is more likely with increased behavior capability, and behavior capability is strengthened through goal setting, skill building and self-monitoring [51]. Also important are confidence in one's ability to perform a given behavior (self-efficacy) and expectation of favorable outcomes of the behavior (outcome expectations). Behavioral strategies may vary by stage of change (i.e., experiential processes during initial phases of behavioral adoption and behavioral processes occurring during action and maintenance phases) [52]. In addition, the BE WELL intervention draws upon key research evidence for the importance of self-management in chronic disease management [53-55]. Successful self-management intervention is driven by patient-defined problems and fosters the mastery of skills in problem solving, action planning, decision making, and support building through an iterative process [55,56].

Furthermore, the BE WELL intervention is based on the premise that long-term changes in diet and exercise and sustained motivation to maintain behavior changes are most likely to occur when the strategies used to motivate and support behavior change are flexible, sensitive to cultural and individual differences, and broadly acceptable to those in the target population. We make use of a combination of a structured protocol (in which all participants receive certain common core information) and individually tailored strategies to help each participant achieve and maintain specific physical activity and dietary changes directed toward the overall intervention goals of losing weight and increasing physical activity.

The BE WELL intervention clearly differs from the delivery of lifestyle modifications in the usual primary care setting. Current practice routinely involves physician advice, occasionally with referral to a dietitian who takes a diet history and who then provides standard educational materials and advice during a small number of individual or group sessions, typically with little or no follow-up. This standard clinical approach lacks the theoretical basis and behavioral self-management focus described above.

#### Evidence-based Intervention Goals

A goal-based approach is used in the BE WELL intervention in which participants will be given the same weight loss and physical activity goals. The weight goal is to achieve and maintain a weight loss of 7% of baseline body weight in a gradual stepwise fashion. A 7% weight loss has proven to be feasible and safe and is associated with clinically significant reductions in the risk of diabetes and cardiovascular disease [57-60]. Participants who wish to lose more than 7% of their starting weight may be encouraged to do so only insofar as the participant maintains a normal BMI at or above 21 and the rate of weight loss does not exceed three pounds per week. The physical activity goal is to achieve and maintain a minimum of 150 minutes per week of moderate intensity physical activity (such as brisk walking). This goal is consistent with the new Physical Activity Guidelines for Americans [61], and is deemed safe and attainable for most adults, including those with chronic conditions such as asthma. Participants, especially those who are habitually sedentary, will be advised to gradually and steadily increase daily walking with a goal of achieving 150 minutes of brisk walking per week by the end of the Intensive intervention stage in month 4. Regular physical activity recommendations for activities of moderate intensity other than brisk walking, as well as strength and flexibility physical activities, will be tailored to the participant's situation [62,63]. After attaining the minimum goal of 150 minutes per week, participants who wish to be more active will be encouraged to do so, as tolerated. If participants reach the 150-minute goal but are not achieving the weight goal, they will be encouraged to further gradually increase their physical activity to 60 minutes/day of moderate physical activity [62,64,65] as well as to consider further calorie restriction.

To help them achieve and maintain the weight goal, participants also will be given a goal for daily calories. A moderate reduction of caloric intake by 500-1000 kcal/day has been shown to produce clinically significant weight loss over time and is a safe and achievable goal for most people [27]. Of note, the calorie goals will be given as a means to achieve and maintain the weight goal, rather than as a goal in and of itself. Therefore, if a participant consumes more than the assigned calorie goal, but is achieving the weight goal, there is no need to focus on further reductions. Participants will be encouraged to gradually achieve the calorie goals through portion control, choices of low-energy and nutrient-dense meals and snacks, healthy food preparation techniques, and careful selection of restaurants, including fast food, and of the items offered. Participants also will be advised to: (1) lower saturated fat intake to <10% of caloric intake, (2) lower cholesterol intake to <300 mg/day, (3) consume a high plant-based diet that includes a variety of vegetables, beans, whole grains, low-fat dairy products, and whole fruits, and (4) reduce intake of high glycemic index carbohydrates.

